## EFFECTIVENESS OF STEROIDS IN PREVENTING UPPER AIRWAY OBSTRUCTION AFTER EXTUBATION IN CRITICALLY-ILL CHILDREN.

A recent meta-analysis [7] of studies in adult patients with and without UAO risk factors receiving different regimens of steroids showed that steroids reduce the incidence of upper airway complications and reintubation in high-risk patients.

Studies in pediatric patients are based on widely heterogeneous samples of patients, doses and timing of prophylactic therapy ranging from one hour to 24 hours prior to extubation [4,7].

In studies on the use of dexamethasone in children, a variety of regimens have been used versus placebo. Some authors report a decrease in the incidence of stridor [5,8], whereas two studies show a reduction in the incidence of reintubation [8,9]. A study in neonates concluded that dexamethasone reduced the risk for reintubation [10]. In contrast, this benefit has not been proven in other studies in children [11] and neonates [12].

Baranwal et al [3] compared two regimens in high-risk pediatric patients: starting dexamethasone therapy 6 hours vs 24 hours before extubation. The authors found that the 24-h regimen reduced significantly the incidence of UAO, as compared to the 6-h regimen.

A Cochrane's systematic review [4] concluded that the effectiveness of steroids in preventing UAO in children has not been sufficiently demonstrated, and further studies are needed to assess its potential benefits, especially in high-risk patients.

In light of the lack of consistent evidence, we have designed a randomized study to compare the effectiveness of dexamethasone vs placebo in the prevention of post-extubation UAO in high-risk pediatric patients (> 48 hours intubated).

The main objective of this study is to explore whether dexamethasone is effective in preventing and reducing the severity of UAO symptoms in critically-ill children vs. placebo. Secondary objectives include investigating whether dexamethasone reduces the incidence of reintubation and evaluating the potential secondary effects associated with this medication.

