## **INTERVENTION**

The treatment group will receive intravenous 0.25 mg/kg/dose (to a maximum of 8 mg) every 6 hours, for a total of 4 doses. The first dose will be administered between 6 and 12 hours prior to extubation. The placebo group will be administered saline 0.9%. The study medication will have the same aspect and characteristics than placebo and both will be administered in the same way.

|                                                                                                                      |
|----------------------------------------------------------------------------------------------------------------------|
| EFFECTIVENESS OF STEROIDS IN PREVENTING UPPER AIRWAY OBSTRUCTION AFTER EXTUBATION IN CRITICALLY-ILL CHILDREN. |
|----------------------------------------------------------------------------------------------------------------------|

Dose adjustment, discontinuance or reinitiation of treatment will not be allowed. Inspections will be performed to ensure that the treatment is being administered adequately.

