### **DATA COLLECTION AND ASSESSMENT OF EFFICACY**

On inclusion, demographic (age, sex and weight) and clinical data will be collected, as follows:

- Diagnosis (six diagnostic groups will be established): surgery, lower airway obstruction, neurological disease, sepsis, trauma and other diagnosis.
- Assessment of severity: the clinical status of the patient will be assessed using PIM2, PRIMS 3 and PELOD scores prior to extubation.
- Size and type of endotracheal tube (cuffed or uncuffed).
- Route of intubation (oral, nasal).
- Previous need for endotracheal tube replacement.
- Previous airway endoscopies.
- Respiratory infection confirmed by endotracheal aspirate culture.
- Presence of blood in endotracheal aspirate.
- Duration of endotracheal intubation prior to extubation (days).

The primary endpoint is the reduction of the incidence of moderate to severe UAO symptoms within 48 hours after extubation. Moderate-severe UAO symptoms will be considered if stridor or Taussig score >5 are present. The secondary endpoints are the presence of reintubation and the potential secondary effects associated with dexamethasone.

|                                                                                                               |
|---------------------------------------------------------------------------------------------------------------|
| EFFECTIVENESS OF STEROIDS IN PREVENTING UPPER AIRWAY OBSTRUCTION AFTER EXTUBATION IN CRITICALLY-ILL CHILDREN. |
|---------------------------------------------------------------------------------------------------------------|

A record of the following variables will be kept at 15 minutes, 1h, 2h, 6h, 12h, 24h and 48 hours after extubation:

1. UAO Taussig score[13], a clinical scoring system for the assessment of UAO severity; evaluating stridor, retractions, inflow of air into the lungs, cyanosis and consciousness (table 1). Presence of inspiratory stridor.
2. Need for and frequency of additional therapies for respiratory distress: adrenaline or nebulized budesonide, intravenous steroids, heliox or non-invasive ventilation.
3. Hemodynamic (blood pressure, heart rate) and respiratory (peripheral oxygen saturation, respiratory rate) parameters.
4. Arterial pCO2 and pO2 and glycemia. Blood samples will not be routinely collected, they will be drawn only for clinical purpose.
5. Need for reintubation, time point and cause.
6. Presence of digestive bleeding.
7. Occurrence of infection.

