## **STATISTICS**

Categorical variables will be expressed as frequencies and percentages. Normality of continuous data will be assessed by the Kolmogorov-Smirnov test. Continuous variables will be expressed as mean values and SD, or as median values and interquartile range.

To compare the primary endpoint of outcome between the group receiving dexamethasone and the group receiving placebo Z-test statistics will be used. Per protocol analysis will be performed. An intention-to-treat analysis will be also performed to guarantee the effect of randomization.

The association between other categorical variables will be assessed by Chi-squared test or Pearson's coefficient, or by Fisher's exact test, as appropriate, based on the sample size. Continuous variables will be compared by Student's t-test or Mann-Whitney U test. In comparisons of values with respect to time, Student's t-test of repeated measures or Wilcoxon test will be performed, as appropriate. Additional subgroup analysis according to age and pathologies will be performed.

Bilateral statistical tests will be used at a 5% level of significance. Statistical analysis will be performed using SPSS version 20 (SPSS Inc, Chicago, USA).

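### The protocol lists per-protocol before intention-to-treat for the primary comparison of a superiority trial and does not say which decides

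*Protocol*

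**What the plan says.** The main objective is to "explore whether dexamethasone is effective in preventing and reducing the severity of UAO symptoms in critically-ill children vs. placebo". The sample size is for a two-sided comparison of 0.33 with 0.16, and no non-inferiority margin appears anywhere, so this is a superiority trial.

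The Statistics section first names the test: "To compare the primary endpoint of outcome between the group receiving dexamethasone and the group receiving placebo Z-test statistics will be used". The next two sentences are: "Per protocol analysis will be performed. An intention-to-treat analysis will be also performed to guarantee the effect of randomization". No other section ranks the two analyses or defines the per-protocol set.

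On treatment, the Intervention section gives four doses at 6-hour intervals and adds: "The first dose will be administered between 6 and 12 hours prior to extubation". It also says: "Dose adjustment, discontinuance or reinitiation of treatment will not be allowed". The primary endpoint covers the 48 hours after extubation. Over the same period the protocol records reintubation and additional therapies, among them "intravenous steroids, heliox or non-invasive ventilation". The data collection section also says that interventions a patient needs are allowed, and that those affecting the upper airway are recorded and considered in the analysis.

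**The concern.** In a superiority trial the analysis of all randomised children as assigned is the one that randomisation protects. A per-protocol analysis compares children selected after randomisation. The protocol itself gives preservation of randomisation as the reason for the intention-to-treat analysis, yet lists that analysis second and introduces it as an addition.

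The order matters more here than in a trial where treatment ends before the outcome can occur. Part of the course is given after extubation, when the outcome is already being counted. A child who obstructs early may be reintubated or given rescue steroids, and may then miss or depart from the remaining study doses. If such children are left out of the per-protocol set, the outcome has helped to decide who is analysed. Equal exclusion of events in both arms costs power. Unequal exclusion biases the comparison in either direction. With no decisive analysis named, two results for the primary endpoint will exist, and the choice between them could follow the data.

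**Working it through.** **1. The plan's own figure.** Inputs from the Sample Size section: 0.33 vs 0.16, Cohen's h = 0.4, two-sided 5%, 80% power, 10% loss.

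- h = 2·asin(√0.33) − 2·asin(√0.16) = 0.4008, stated as 0.4.
- n = 2·((1.960 + 0.842)/0.4)² = 98.1, so 99 per arm.
- 99/(1 − 0.10) = 110 per arm.

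The stated 110 reproduces and already includes the loss. The point is not about a wrong sample size.

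**2. Dose timing.** Counting from the first dose, doses fall at 0, 6, 12 and 18 h, and extubation falls at 6 to 12 h.

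| Extubation at | Doses relative to extubation |
|---|---|
| 6 h | −6, 0, +6, +12 h |
| 12 h | −12, −6, 0, +6 h |

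The last dose is therefore always 6 to 12 h after extubation, inside the 48-hour window. Completion of treatment cannot be known before the outcome period starts.

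**3. Effect of excluding children with events.** The documents give no exclusion rates, so those below are assumptions, shown as a range. Take 99 evaluable children per arm. If a fraction f of the children with events is excluded, and nobody else, an event rate p becomes p(1 − f)/(1 − pf) and the arm shrinks to 99(1 − pf). The chance that the pooled two-proportion Z-test is significant was found by summing binomial probabilities over all possible results, with arm sizes rounded to whole children.

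*Planned effect, equal exclusion in both arms:*

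| f | Placebo rate (n) | Dexamethasone rate (n) | Power |
|---|---|---|---|
| 0 | 0.330 (99) | 0.160 (99) | 80.8% |
| 10% | 0.307 (96) | 0.146 (97) | 77% |
| 20% | 0.283 (92) | 0.132 (96) | 74% |
| 30% | 0.256 (89) | 0.118 (94) | 68.7% |

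For example, at f = 30%: 0.33 × 0.7/(1 − 0.099) = 0.231/0.901 = 0.256.

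*No true effect, 0.33 in both arms (0.33 × 99 = 32.7 events expected per arm):*

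| Placebo events excluded | Dexamethasone events excluded | Rates compared | False benefit (one-sided) |
|---|---|---|---|
| 0% | 0% | 0.330 vs 0.330 | 2.5% |
| equal, 10% to 40% | equal, 10% to 40% | equal | about 2.5% |
| 10% (3.3 children) | 15% (4.9 children) | 0.307 vs 0.295 | 3.8% |
| 10% (3.3 children) | 20% (6.5 children) | 0.307 vs 0.283 | 5.5% |
| 10% (3.3 children) | 40% (13.1 children) | 0.307 vs 0.228 | 22% |

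Swapping the arms in the last row gives 22% false harm.

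**4. What intention-to-treat costs.** By the arcsine method, power = Φ(h·√(n/2) − 1.960). This is 84.4% with all 110 per arm analysed and 80.5% with 99. Suppose, as an assumption, that 5%, 10% or 15% of the dexamethasone arm has the placebo rate through non-adherence. The dexamethasone rate becomes 0.1685, 0.177 or 0.1855, and power with 110 per arm is 80.0%, 75.0% or 69.6%.

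**The case against.** A reader might infer that the protocol makes per-protocol its primary analysis. It does not say so. It plans both analyses and calls neither primary. The lead role is read from the order of two sentences and one adverb. That stands, so the supportable statement is that the deciding analysis is not named and the wording leans towards per-protocol.

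A reader might also infer that children are to be excluded because of their outcome. The documents do not support that. The per-protocol set is not defined in the protocol and may be defined in a statistical analysis plan. If it rested on eligibility or on the doses given before extubation, the mechanism would largely disappear. Needed interventions are expressly allowed, so rescue steroids are not a stated deviation. No section says that obstruction or reintubation stops the study doses, discontinuance is not permitted, and administration is checked every shift. The dose timing shows that dependence on the outcome is possible, and no more.

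The 22% figure is an extreme. It needs four times as large a share of events excluded on dexamethasone as on placebo while the drug has no effect. The treatment is double-blind with matching placebo. With no effect, exclusions driven only by obstruction should be about equal in the two arms, which keeps the one-sided error near 2.5%. Blinding does not remove the loss of power, and a real drug effect or side effect could make exclusions differ by arm.

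An unseen statistical analysis plan does not remove the point. It could define the set, but if it named intention-to-treat as primary, the order in the protocol would still need to be aligned with it.

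**Conclusion.** The point holds in limited form. For the primary comparison of a superiority trial, the protocol lists the more bias-prone analysis first, adds intention-to-treat second, and does not say which decides. The dosing schedule makes outcome-dependent membership of the per-protocol set possible, but nothing in the document makes it a rule.

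The size depends on assumed exclusion rates. With 10% to 30% of events excluded equally, power falls from 81% to between 77% and 69% with no inflation of error. With modest imbalance (10% vs 15% or 20%) the one-sided error is 3.8% to 5.5%, and it reaches 22% only at 10% vs 40%. Because the intention-to-treat analysis is already planned, an analysis that keeps the randomised groups will exist, and the harm is limited to which result is taken as decisive. This should be fixed but does not threaten the trial.

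**What to change.** Replace the two sentences in the Statistics section with wording such as: *The primary analysis of the primary endpoint is by intention to treat: all randomised children, analysed in the arm to which they were assigned, whatever study doses or rescue treatment they received. The per-protocol analysis is a supportive sensitivity analysis.* This should be settled before unblinding.

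The cost is wording only, and the sample size stays at 110 per arm. The downside is that non-adherent children stay in and may dilute the observed effect, as the last step of the working shows.

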## **STUDY POPULATION**

The sample will include children between 1 month and 16 years of age admitted to the ICU who require intubation for more than 48 hours, regardless of their condition. Patients with airway malformations, suspected or confirmed croup syndrome, tracheitis or epiglottitis and those who had previously underwent any surgery involving upper or lower airway will be excluded. Furthermore, other exclusion criteria were the administration of steroid therapy within the last seven days, patients who had a previous extubation failure during the stay or refusal to participate in the study.

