|--------------------------------------------------------------------------------------------------------------------------------------------|

| Tests                                          | Screening | First visit prior to extubation | Visits 2 to 8 |
|------------------------------------------------|-----------|---------------------------------|---------------|
| Assessment of eligibility               |           |                                 |               |
| Informed consent                               | X         |                                 |               |
| Inclusion and exclusion criteria               | X         |                                 |               |
| Anamnesis                                      | X         |                                 |               |
| Assessment of safety                    |           |                                 |               |
| Physical examination                           | X         | X                               | X             |
| Vital signs                                    | X         | X                               | X             |
| Assessment of adverse events                   |           | X                               | X             |
| Previous and current medications               | X         | X                               | X             |
| Assessment of efficacy a     |           |                                 |               |
| Vital signs                                    | X         | X                               | X             |
| Stridor                                        | X         | X                               | X             |
| Taussig scale                                  | X         | X                               | X             |
| Reintubation                                   |           | X                               | X             |
| Other assessments                       |           |                                 |               |
| Other medications                              |           | X                               | X             |
| Deliveries of medication                |           |                                 |               |
| Randomization and dispensing of the medication |           | X                               | X             |

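### The only between-arm tests named for vital signs use neither age nor a baseline reading, which costs precision across ages 1 month to 16 years

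*Protocol*

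**What the plan says.** The Statistics section of the protocol gives a general rule for continuous data: "Continuous variables will be compared by Student's t-test or Mann-Whitney U test". Two further sentences bear on the point. One concerns change over time: "In comparisons of values with respect to time, Student's t-test of repeated measures or Wilcoxon test will be performed, as appropriate". The other concerns subgroups: "Additional subgroup analysis according to age and pathologies will be performed". No age bands are given, and the variables to be examined by subgroup are not named.

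The data-collection section lists, among the items recorded at seven times from 15 minutes to 48 hours after extubation, "Hemodynamic (blood pressure, heart rate) and respiratory (peripheral oxygen saturation, respiratory rate) parameters". In Table 2 vital signs are marked at screening, at the first visit prior to extubation and at visits 2 to 8. The row appears under "Assessment of safety" and again under efficacy. The eligible population is "children between 1 month and 16 years of age admitted to the ICU". The side effects of dexamethasone are a secondary objective and a secondary endpoint, but blood pressure and heart rate are not named individually as endpoints.

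**The concern.** Normal blood pressure, heart rate and respiratory rate change with age throughout childhood. A two-sample test on values pooled from infants and adolescents therefore carries the whole age spread as noise, and the pooled mean is hard to interpret clinically. Much of that spread is predictable from age and an early reading, both of which the trial already collects.

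The other two methods do not repair this. A paired test compares each child with himself. Vital signs may move after extubation in either arm, so significance in one arm and not in the other is not a test of dexamethasone against placebo. Age subgroups narrow the spread within each comparison, but they cut the number of children in it and give no overall adjusted estimate.

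What is at stake is a safety comparison. A modest haemodynamic effect could be reported as no difference when the test had limited power to show it.

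**Working it through.** **Step 1. Evaluable number per arm.** The Sample size section gives proportions of 0.33 and 0.16, h = 0.4, 80% power, two-sided 5%, 110 per arm and 10% loss.
- n = 2 × ((1.96 + 0.8416) / 0.40)² = 98.1, rounded up to 99.
- 99 / (1 − 0.10) = 110.

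So 110 reproduces as a figure that already contains the loss, leaving 99 evaluable per arm. The plan states no power for any vital sign.

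**Step 2. Formulas.** Work in units of the SD of the pooled values, at a single visit, with ρ the correlation between the outcome and the baseline information used for adjustment. ρ is an assumption; the documents give none.
- SE = √(2/99) × √(1 − ρ²) = 0.1421 × √(1 − ρ²).
- Detectable difference at 80% power = 2.8016 × SE.
- Power for a 0.3 SD difference = Φ(0.3/SE − 1.96).

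| Analysis | √(1 − ρ²) | Detectable difference (SD) | Power for 0.3 SD |
|---|---|---|---|
| Unadjusted | 1 | 0.398 | 56% |
| Adjusted, ρ = 0.5 | 0.866 | 0.345 | 68% |
| Adjusted, ρ = 0.7 | 0.714 | 0.284 | 84% |
| Adjusted, ρ = 0.8 | 0.600 | 0.239 | 94% |

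For example, unadjusted: 0.3 / 0.1421 = 2.11; 2.11 − 1.96 = 0.15; Φ(0.15) = 0.56. If all 110 per arm were evaluable, the first three powers would be 60%, 73% and 88%.

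**Step 3. On a measurement scale.** Assume a pooled systolic SD of 18 mmHg, so SE = 18 × 0.1421 = 2.56 mmHg.
- 5 mmHg, unadjusted: 5/2.56 − 1.96 ≈ 0, so power is about 50%.
- 5 mmHg, with 25%, 40%, 50% or 60% of the variance explained: 62%, 71%, 79% or 87%.
- 10 mmHg, unadjusted: 10/2.56 − 1.96 = 1.95, so power is about 97%.

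Over other assumed SDs:

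| Assumed SD | 5 units, unadjusted | 5 units, ρ = 0.7 | 10 units, unadjusted |
|---|---|---|---|
| 15 | 65% | 91% | 99.7% |
| 20 | 42% | 69% | 94% |
| 25 | 29% | 50% | 80% |

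**Step 4. Which reading can serve as baseline.** The Intervention section places the first dose 6 to 12 hours before extubation. Table 2 puts randomisation and dispensing at the first visit prior to extubation and does not say whether vital signs are read before the dose. That reading may therefore already carry a drug effect, and adjusting for it could remove part of what is being measured. The screening visit carries no randomisation or dispensing mark in Table 2, so its reading comes before treatment.

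**The case against.** **This is detail for an analysis plan.** Covariates and models for supportive vital signs are often settled there, and a plan may exist that is not at hand. That lowers the priority. It does not remove the point, because the protocol does not leave the method open: it names the tests, and neither takes a covariate.

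**The protocol does not say that raw values are compared.** True. That is inferred from a general sentence, and a t-test on change from baseline or on age-standardised values would fit the wording. No such value is named, however. A t-test on change would also be a partial answer: its detectable difference is 2.8016 × √(2/99) × √(2(1 − ρ)), which is 0.398 SD at ρ = 0.5 (no gain over the unadjusted test) and 0.308 SD at ρ = 0.7 (against 0.284 with ANCOVA).

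**Age is not ignored, and safety does not rest on these tests alone.** Both hold. Age subgroups are planned, and severe adverse events are judged on the individual patient's clinical status, so an important rise in one child can be caught that way. Neither gives an adjusted comparison between arms.

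**A reader might infer that age variation swamps any steroid effect, or that chance age imbalance invalidates the comparison.** The documents support neither. They give no SD, correlation or expected effect from which swamping could be shown, and a 10-unit difference keeps 80% power or more over the SDs tried. Under randomisation the unadjusted test is unbiased, and its standard error already allows for chance imbalance in age.

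**Conclusion.** The point holds as a loss of precision. The between-arm tests named for continuous variables leave out age and the baseline reading, and nothing else in the Statistics section supplies an adjusted comparison between arms. For a 0.3 SD difference the gain forgone is about 12 percentage points of power at ρ = 0.5 and 28 at ρ = 0.7. These figures assume 99 evaluable per arm, one visit at a time and the stated correlations. A screening reading taken long before extubation may correlate less well than a later one, in which case more of the gain would have to come from age.

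It would go too far to conclude that a real effect would probably be missed: at the assumed SD of 18 mmHg, power for 5 mmHg is about even, and for 10 mmHg it is high. The priority is minor to moderate. Blood pressure, heart rate and respiratory rate are supportive safety measures, and the analyses of the primary endpoint and of reintubation are untouched.

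**What to change.** For blood pressure, heart rate and respiratory rate, replace the general rule with one between-arm analysis over visits 2 to 8: a repeated-measures model, or ANCOVA at stated visits. Adjust it for age, or use age-standardised values, and for a reading taken before the first dose, such as the screening value. Report the adjusted difference between arms with its confidence interval.

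State that a pre-extubation reading is not used as the covariate unless it is known to precede the first dose. State also that within-arm paired tests are descriptive and are not used to judge a drug effect.

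The change is to analysis wording only: age and screening vital signs are already collected. The cost is slightly more analysis work and, if z-scores are used, the choice of an age reference, which should be named in advance.

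### Reducing severity is part of the main objective, but the Protocol names no graded severity endpoint, and its only stated method for values over time is a within-patient test that does not compare the arms

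*Protocol*

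**What the plan says.** The objectives paragraph that closes the Protocol's background states: "The main objective of this study is to explore whether dexamethasone is effective in preventing and reducing the severity of UAO symptoms", with placebo as the comparator.

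Under Data Collection and Assessment of Efficacy, the endpoint is one of incidence: "The primary endpoint is the reduction of the incidence of moderate to severe UAO symptoms within 48 hours after extubation". A child counts as an event if stridor is present or the Taussig score exceeds 5. The secondary endpoints are reintubation and side effects of dexamethasone. The same section introduces the Taussig score as "a clinical scoring system for the assessment of UAO severity" and puts it first among the variables to be recorded at "15 minutes, 1h, 2h, 6h, 12h, 24h and 48 hours after extubation".

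In the Statistics section, the primary comparison is "between the group receiving dexamethasone and the group receiving placebo Z-test statistics will be used". Continuous variables are compared by Student's t-test or Mann-Whitney U. For comparisons of values over time, a Student's "t-test of repeated measures or Wilcoxon test will be performed, as appropriate". All tests are two-sided at 5%.

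**The concern.** An objective that names severity needs a result that grades severity and compares the arms. The Protocol collects the data for one but does not define it. The one method it fixes for values over time measures change within a child. UAO may well change over 48 hours in both arms, so a significant within-arm change says nothing about the drug.

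Two things are at stake. With no severity comparison defined, a severity claim could be drawn from one arm changing significantly and the other not, or from whichever recording time shows a difference. And a drug that turns severe obstruction into mild stridor could go unseen in the primary result.

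**Working it through.** **Objective against endpoints.** The objective has two parts, prevention and reduced severity. Prevention maps to the binary primary endpoint and its single Z-test. Severity maps to no named endpoint.

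**What the binary endpoint can see.** Table 1 scores five items from 0 to 3, so the total runs from 0 to 15, and mild stridor alone scores 1. The endpoint definition counts stridor or a score above 5. Read literally, a child with mild stridor and a total of 1 is the same event as a child in severe obstruction. A shift from severe to mild stridor would leave the count unchanged.

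**Which listed test compares the arms.** The repeated-measures t-test is a paired test. Mann-Whitney is listed separately, so the Wilcoxon test here is the signed-rank test. Both test change between two times in the same children. The between-arm t-test or Mann-Whitney test is available, but no time point or summary of the seven scores is attached to it.

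**The plan's own figure.** Inputs from Sample Size: h = 0.4, 80% power, 5% two-sided, 10% loss.
- n = 2 × ((1.960 + 0.842) / 0.4)² = 98.1, rounded up to 99 per arm.
- 99 / 0.9 = 110 per arm, as stated. With h unrounded at 0.4008, the result is 98, then 109.

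This figure is sized on the binary endpoint, so nothing below alters it.

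**If within-arm significance were compared between arms.** Assume the same true change in both arms, independent arms, and power w for the paired test within each arm. The chance that exactly one arm is significant is 2w(1 − w):

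| Within-arm power w | Exactly one arm significant | Dexamethasone only |
|---|---|---|
| 5% | 9.5% | 4.75% |
| 20% | 32% | 16% |
| 50% | 50% | 25% |
| 80% | 32% | 16% |
| 95% | 9.5% | 4.75% |

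**If the score were tested between arms at each of the seven times at 5%.** With independent tests, the family-wise error is 1 − 0.95⁷ = 30.2%. With correlated tests, simulating seven normal test statistics (200,000 replicates) gives:

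| Assumed correlation | Common to all pairs | Decaying with lag, AR(1) |
|---|---|---|
| 0.5 | 23% | 27% |
| 0.7 | 18% | 22% |
| 0.8 | 15% | 19% |
| 0.9 | 12% | 15% |

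One pre-specified comparison holds 5%. Bonferroni over seven would need 0.05 / 7 = 0.0071 each.

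**Reintubated children.** The Background puts reintubation at 6% to 13%. If that applied to all children, it would be 0.06 × 110 = 6.6 to 0.13 × 110 = 14.3 per arm. If it applied only to those with obstruction (0.33 × 110 = 36.3 in the placebo arm), it would be 2.2 to 4.7. These children have no meaningful later post-extubation score and are among the worst cases, so a severity summary must give them a place.

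**The case against.** The case against is substantial, and several parts of it stand.

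- A reader might infer that the plan assigns the severity objective to the paired tests. It does not. The sentence names no variable and could equally cover vital signs or blood gases, and nothing says a within-arm p-value will serve as evidence against placebo.
- A reader might infer seven separate between-arm tests. The seven times are a recording schedule; no text says a test is repeated at each.
- A reader might conclude that severity has no valid test. That is too strong. The primary endpoint is intended as a moderate-to-severe threshold and is tested once between arms, so it bears on severity in part. A between-arm Mann-Whitney test is also among the listed methods.
- A reader might multiply eight repeated variables by seven times to get 56 tests and 2.8 expected false positives. This fails because three of the eight (pCO2, pO2, glycaemia) come from blood samples that the Protocol says are not routine. The remaining five give at most 35 tests and 35 × 0.05 = 1.75, and four of those five are vital signs, not severity measures.
- Reintubation is not ignored. The Protocol says such events will be allowed for in the analysis, records their timing and cause, and makes reintubation a secondary endpoint.
- A summary measure, a multiplicity rule and the handling of reintubated children are often left to a statistical analysis plan, which is not shown.

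The last argument does not dispose of the point. The Protocol itself lists the endpoints and itself fixes the paired tests. A later plan that followed that text would still lack a graded severity endpoint, and the stated method for values over time would still not compare the arms.

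**Conclusion.** The point holds as a gap between objective, endpoint and method. Severity is in the main objective; no graded severity endpoint is named; the one method fixed for values over time cannot compare dexamethasone with placebo; and the between-arm test on offer is tied to no time or summary.

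The sizes are conditional on how the gap is filled: about 10% to 50% discordant arms if within-arm significance is compared, and about 12% to 30% family-wise error if the score is tested at all seven times. The within-arm powers (5% to 95%) and correlations (0 to 0.9) are assumptions, since the Protocol gives neither. The documents do not show that either route is planned, so these figures describe exposure and not a stated error. The primary 5% test and the 110 per arm are unaffected. This is an inexpensive improvement and not a threat to the main result.

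**What to change.** In Data Collection and Assessment of Efficacy, add one secondary severity outcome: the peak modified Taussig score within 48 hours of extubation, with reintubation for UAO ranked worse than any score. State how reintubation for other causes is treated. In Statistics, compare it once between arms by Mann-Whitney or a proportional-odds model.

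For the other routinely repeated variables (blood pressure, heart rate, oxygen saturation, respiratory rate), replace the paired tests with one mixed model per variable containing arm, time and arm-by-time, labelled descriptive.

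The cost is wording and slightly more analysis work. The scores and the timing and cause of reintubation are already collected, the stated software fits these models, and no further children are needed. The drawback is that the new outcome overlaps with both the primary endpoint and reintubation, so it should be read as supporting them and not as independent evidence.
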